## Introduction

### Early Discharge From the Hospital

In the last two decades, the hospital stay following surgical procedures has been shortened drastically, due to recovery-enhancing strategies such as the use of minimally invasive techniques and the implementation of fast-track programs [1-4]. The advantages of early postoperative discharge include increased patient satisfaction, low hospital-acquired infection rates, and reduced hospitalization costs [5]. However, a major disadvantage of minimizing the length of a hospitalization is that patient contact becomes very brief, which is often at the expense of time spent on patient education. Ironically, the lack of detailed convalescence instructions at the time of discharge increases the risk of an unnecessary prolonged recovery [6-11]. Therefore, as long as the organization of perioperative care has not fully anticipated the transition of postoperative recovery to the home setting, early discharge does not necessarily translate into accelerated recovery and earlier resumption of (work) activities [12-14].

In gynecology, the postoperative convalescence after discharge from the hospital has not received much attention in research and practice. Yet, there is considerable evidence that the length of recovery time after a gynecological surgery systematically exceeds the period considered as appropriate by specialists [5,10,12-17]. In a prospective study performed by our own study group among 148 patients receiving gynecological surgery for a benign disease, median time to return to work (RTW) exceeded the recommended sick leave of 6 weeks by approximately 3 weeks. The median time to RTW following an intermediate surgery (eg, laparoscopic or vaginal hysterectomy) was 60 days (interquartile range, IQR 56-135) and following a major surgery (eg, abdominal hysterectomy) 69 days (IQR 56-135) [10].

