##### Occupational Intervention

The occupational intervention is developed to provide additional guidance to those patients at risk for prolonged sick leave. The occupational intervention will be delivered by a group of six independent OPs, who will be trained as RTW coordinators before the start of the trial. There are two types of consultations: (1) a preoperative, and (2) a postoperative consultation. All consultations will be delivered by telephone, unless the OP and the patient decide together otherwise.

The patients who have an inadequate expectation about their own recovery (longer than 3 weeks for LAS, longer than 6 weeks for VH/TLH, or longer than 8 weeks for TAH), or have a low intention to resume work activities while still recovering, are offered a preoperative consultation, as expectations about RTW and intention to resume work have been identified as two predictors for RTW in recent studies [10,40,41]. During the preoperative consultation, the OP explains the importance of a prosperous recovery in terms of improving quality of life and preventing long term sickness. In addition, the OP tries to identify and—if necessary—alter attitudes and (irrational) beliefs about recovery.

The patients who exceed 5 weeks of sick leave receive a postoperative consultation, during which, the OP assesses the underlying mechanism for the delayed recovery. The OP gives advice to improve the reintegration process. Moreover, as a RTW coordinator, the OP has an excellent position to communicate with the patient’s gynecologist, GP, OP, and employer, if necessary, and of course, with the consent of the patient, stimulating an integrated care approach. In addition, the OP has the possibility to initiate a participatory workplace intervention, aimed at finding consensus between the patient and her employer concerning solutions for identified obstacles for RTW with the help of an occupational therapist (OT) [42,43].

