### Sample Size

We calculated the sample size needed with the method described by Hussey and Hughes [35]. Based on the previous study, we expect a hazard ratio of 1.5 on the primary outcome full sustainable RTW. To achieve a power of 0.8 with a two-tailed alpha of .05, and taking into account a dropout rate of 10%, a total of 212 patients will be needed when using the log-rank test.

With an intracluster correlation of .05, 9 clusters, and 10 time periods, the design effect is calculated to be 2.14 [35]. By multiplying the design effect by the sample size without a correction for a stepped wedge design, a sample size of 454 women is needed. Assuming that all of the hospitals will include the same amount of participants, each hospital should include approximately 50 patients (5 patients per time period per hospital).

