### Statistical Analyses

#### Effect Evaluation

All further described analyses will be performed at the patient level, according to the intention-to-treat principle. In addition, for all tests, a two-tailed significance level of *P*≤.05 will be considered statistically significant. The statistical software packages that will be used include SPSS (version 16.0) and STATA (version 11.2).

The baseline characteristics will be summarized using descriptive statistics, and compared between the experimental and control group to verify prognostic comparability. In case of coincidental and meaningful differences, these variables will be used as covariates in the further described models.

For the primary outcome, the duration of sick leave until full sustainable RTW, Cox regression analyses will be used to investigate the intervention effect. Both the crude and adjusted analyses will be performed. In the adjusted analyses, the following variables will be used as covariates: (1) hospital, to adjust for clustering (random gamma effect); (2) type of surgery performed; (3) time period, to adjust for naturally occurring changes over time irrespective of the intervention; and (4) optionally, (time period) x (intervention) interaction term, to adjust for time effects (the longer the care program is implemented, the more effective it might be).

The differences in secondary outcomes will be assessed using generalized linear longitudinal mixed models. All of the available measurements (2 weeks, 6 weeks, 12 weeks, 26 weeks, and 52 weeks) will be used, and the baseline scores will be used as covariates, as well as the hospital and the type of surgery (random effect).

To assess whether protocol deviations caused bias, a per protocol analysis will be performed, and the results will be compared to the intention-to-treat analyses. In addition, several subgroup analyses will be performed. The predefined subgroups will be: (1) hysterectomy (TAH, VH, TLH); (2) minimally invasive hysterectomy (VH, TLH); (3) abdominal hysterectomy only; and (4) laparoscopic adnexal surgery only.

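### The adjusted primary Cox model assumes proportional return-to-work hazards across surgery types, which the article's own observed times do not fit; stratifying the baseline hazard is a cheap improvement

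*Protocol article*

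**What the plan says.** Under Effect Evaluation, for the duration of sick leave until full sustainable RTW, "Cox regression analyses will be used to investigate the intervention effect", both crude and adjusted. For the adjusted analyses, "the following variables will be used as covariates: (1) hospital, to adjust for clustering (random gamma effect); (2) type of surgery performed", and "time period, to adjust for naturally occurring changes over time irrespective of the intervention". No stratification of the baseline hazard is mentioned.

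Two other places bear on whether surgery types share a proportional hazard:

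- **Introduction, Early Discharge From the Hospital.** In an earlier cohort of 148 patients, median time to RTW after intermediate surgery "was 60 days (interquartile range, IQR 56-135) and following a major surgery (eg, abdominal hysterectomy) 69 days (IQR 56-135". LAS has no observed time.
- **Occupational Intervention.** A preoperative consultation is offered when a patient expects recovery to take "longer than 3 weeks for LAS, longer than 6 weeks for VH/TLH, or longer than 8 weeks for TAH". These are cut-offs for the patient's expectation, not measured times.

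**The concern.** A Cox covariate acts on the hazard by the same factor on every day of follow-up. For surgery type this means that, on any day, patients still on sick leave after abdominal hysterectomy return at a fixed fraction of the rate seen after a lesser procedure. If each operation instead has its own period with few returns, followed by a wave of them, the ratio changes over time and may reverse.

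Surgery type is likely to be one of the strongest predictors of RTW. When a strong predictor is modelled with the wrong time pattern, the model-based variance of the other coefficients, including the program effect, need not be right. At stake are the type I error and interval width of the adjusted primary analysis, and the size of the estimated HR.

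**Working it through.** **1. The planned design.** The sample size assumes that "we expect a hazard ratio of 1.5 on the primary outcome full sustainable RTW". Schoenfeld events are 4 × (1.960 + 0.842)² / (ln 1.5)² = 4 × 7.85 / 0.1644 = 191. Allowing for 10% dropout, 191 / 0.90 = 212.2, against 212 stated. Then 212 × 2.14 = 453.7, against 454 stated. The simulations used 9 hospitals × 10 periods × 5 patients = 450.

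**2. Do the observed times fit proportional hazards?** If they did, S_major(t) = S_intermediate(t)^θ with one θ for all t. The cumulative hazard is H = −ln S.

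| Day | Intermediate | Major | Implied θ |
|---|---|---|---|
| 56 | S = 0.75, H = 0.288 | S = 0.75, H = 0.288 | 1 |
| 60 | S = 0.50, H = 0.693 | S above 0.50, H below 0.693 | below 1 |
| 135 | S = 0.25, H = 1.386 | S = 0.25, H = 1.386 | 1 |

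From day 56 to 60 the intermediate class accumulates 0.693 − 0.288 = 0.405 and the major class less. From day 60 to 135 the intermediate class accumulates 1.386 − 0.693 = 0.693 and the major class more. The hazards must therefore cross, and no single θ fits.

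**3. Do the times suggest a delay?** An exponential curve has its lower quartile at median × ln(4/3)/ln 2 = 0.415 × median, which is day 25 for a median of 60 and day 29 for 69. A Weibull curve with shape 1.5 gives 0.415^(1/1.5) = 0.556 × median, which is day 33 and day 38. The reported lower quartile is day 56 in both classes. In the intermediate class a quarter have returned by day 56, another quarter return in the next four days, and a long tail follows.

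**4. Consequence for the program effect.** Simulated null trials used one hospital crossing per period, 52-week censoring, 10% dropout, period terms and a gamma hospital frailty (variance 0.05, treated as known), with 1,200 to 3,000 runs per case. Assumptions not in the document are a surgery mix of 30/40/30 (LAS, VH/TLH, TAH), medians of 3, 6 and 8 weeks except in the row calibrated to the Introduction, the LAS curve, and the curve shapes. The log-normal spread is (ln 135 − ln 56)/1.349 = 0.652. SD is the actual spread of the estimates.

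| RTW curves | SE/SD, covariate | Type I, covariate | Type I, stratified |
|---|---|---|---|
| Exponential (proportional) | 0.99 | 5.1% | 4.9% |
| Weibull, common shape 1.5 (proportional) | 0.98 | 5.0% | 4.8% |
| Through the Introduction's quartiles | 0.945 | 6.2% | 4.4% |
| Log-normal, spread 1.0 | 0.96 | 5.7% | 4.7% |
| Log-normal, spread 0.65 | 0.93 | 6.9% | 5.1% |
| Weibull shapes rising 1/1.5/2.5 | 0.92 | 7.0% | 5.1% |
| Fixed delay, half the median | 0.88 | 7.7% | 4.7% |
| Log-normal, spread 0.3 | 0.86 | 8.7% | 4.6% |
| Fixed delay, 0.8 of the median | 0.76 | 13.9% | 4.7% |
| Pure shift (extreme) | 0.67 | 19.8% | 4.6% |
| Weibull shapes falling 2.5/1.5/1 | 1.08 | 3.5% | 4.9% |

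Stratified SE/SD is 0.99 in every row. The Monte Carlo error of a 5% rate is √(0.05 × 0.95/1,200) = 0.6 points to √(0.05 × 0.95/3,000) = 0.4 points.

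Separate log-normal simulations (spread 0.65, mix 30/45/25) without a hospital effect gave 8.0% against 5.6% stratified at medians 21/60/69 days, and 7.3% against 5.7% at 21/42/56 days. SE/SD was 0.89 and 0.92, against 0.98 stratified.

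**5. At a true HR of 1.5.** Stratified, the mean estimate is 1.52 throughout. With the covariate it is 1.52 under the proportional Weibull, 1.55 with the Introduction's quartiles, 1.56-1.58 for log-normal curves (spread 0.6 and 0.3) and the half-median delay, and 1.63-1.65 for the two most extreme cases. Stratified power is about 77%. Under the proportional Weibull it is 77.4%, against 77.7% with the covariate.

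**The case against.** **Three stronger readings are tempting, and the document does not support them.**

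- A reader might infer that the 3, 6 and 8 weeks themselves make the hazards non-proportional. They are thresholds for a patient's expectation, and different medians do not break proportionality. The first two table rows use exactly those medians with proportional hazards, and nothing goes wrong. The thresholds show only that recovery is expected on surgery-specific schedules.
- A reader might infer that the SE must be too small. With falling Weibull shapes it is 8% too large. That case does not resemble the Introduction's data, because it gives abdominal hysterectomy an exponential curve with a lower quartile near day 29 for a median of 69. Even so, the article states no hazard shapes.
- A reader might quote larger sizes. A version with hospital as fixed effects reaches 8.4% with SE/SD 0.172/0.197 = 0.87, but stratification there still runs at 6.0%, so part of the excess has another source.

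**The calibration is imperfect.** A log-normal with IQR 56-135 has median √(56 × 135) = 87 days. With medians of 60 and 69 and spread 0.652, the quartiles are about 39-93 and 44-107. The row drawn through the reported quartiles (6.2%, SE 5.5% too small) is closest to the document, and its LAS curve is assumed. The identical IQRs may be a reporting slip.

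**The wording is loose.** The covariate list includes a random hospital effect, and checking proportional hazards is ordinary SAP content. This is fair, and it limits the weight of the point. The article does, however, say how hospital enters and leaves surgery type as a plain covariate. The subgroup analyses limited to abdominal hysterectomy and to LAS avoid the pooling but do not replace the primary test.

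**Conclusion.** The point holds in conditional form. The adjusted model assumes proportional hazards across surgery types. The only observed RTW times, taken as point estimates, do not fit this for the two hysterectomy classes and point to delayed return.

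Under a surgery-specific delay, the SE of the program effect is modestly too small: about 5-10% in most simulations, with type I error about 6-8% and some overstatement of a true HR of 1.5. Larger errors need tighter spreads or near-pure shifts, for which the document gives no evidence. Under proportional curves there is no problem, and under some other shapes the test is conservative.

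The size rests on the assumed surgery mix, the assumed LAS times and curve shapes, and one cohort of 148. This is a cheap improvement to a workable model, not a demonstrated error in the plan.

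**What to change.** Stratify the baseline hazard of the adjusted primary Cox model by the four surgery types instead of entering surgery type as a covariate. Keep the hospital gamma frailty and the time period terms. Do the same for duration until first RTW where a Cox model is used, and for the two subgroups that pool types (all hysterectomies, and minimally invasive hysterectomies).

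The change is one model option and needs no extra data or patients. The article reports that neither data cleaning nor analysis had begun, so it can be fixed without sight of results. The costs are that no HR for surgery type is reported, which the trial's question does not need, and a negligible loss of power (77.7% to 77.4% in the proportional Weibull case).

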### Trial Design

This trial is designed as a cluster, randomized controlled, stepped wedge trial, which involves a sequential rollout of the intervention in the participating clusters over several time periods. In our study, clusters are the departments of obstetrics and gynecology in nine different hospitals in the Netherlands. Each time period (TP) takes 2 months. At the start of the trial (TP_1_), all of the patients scheduled for a surgery in all of the participating hospitals receive usual care (control phase). After two months (TP_2_), the intervention is implemented in the first cluster, and from now on the patients scheduled for a surgery in this hospital will receive the intervention program, while in all of the other hospitals the patients still receive usual care. The patients in cluster 2 who underwent surgery during TP_1_ remain in the control group until they finish the 12 month follow-up. During TP_3_, the intervention program continues in cluster 1, and the intervention is implemented in cluster 2 as well, resulting in the deliverance of the intervention program to the patients in clusters 1 and 2 that will undergo surgery from this point onward, while patients in clusters 3 to 9 serve as the control group. At the beginning of TP_4_, cluster 3 starts with the intervention, etc. This is repeated until the intervention is implemented in all clusters (TP_10_). Figure 1 illustrates the study design.

A cluster design was chosen to minimize the risk of contamination, as our intervention targets both health care providers and patients. A stepped wedge approach was employed because of the unique feature of an unidirectional crossover, preventing the intervention to be withdrawn from the hospital during the trial [34-36]. Because there is substantial evidence from our previous trial that the care program under study will be effective, this is particularly convenient, as hospitals will be able to keep using the intervention after the trial. Moreover, it enables us to study the implementation process carefully, giving valuable insight into barriers and facilitators for future broader implementation.

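### The secondary-outcome mixed models leave out time period, so a calendar trend shared by the hospitals would bias those effects in either direction

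*Protocol article*

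**What the plan says.** All of the model text is in the Protocol article, Effect Evaluation.

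- **Primary outcome.** The adjusted Cox model lists hospital (random gamma effect), type of surgery, and "time period, to adjust for naturally occurring changes over time irrespective of the intervention", with an optional period-by-intervention interaction.
- **Secondary outcomes.** The next paragraph sets a different model: "The differences in secondary outcomes will be assessed using generalized linear longitudinal mixed models". On the data, "All of the available measurements (2 weeks, 6 weeks, 12 weeks, 26 weeks, and 52 weeks) will be used". On adjustment, "the baseline scores will be used as covariates, as well as the hospital and the type of surgery (random effect". Time period is not named, and nothing refers back to the Cox list.
- **Other covariates.** The general rule applies to baseline characteristics compared between the groups: "In case of coincidental and meaningful differences, these variables will be used as covariates in the further described models".

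The rollout is in Trial Design: "Each time period (TP) takes 2 months", one hospital crosses at each step, and "This is repeated until the intervention is implemented in all clusters (TP_10".

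**The concern.** In a stepped wedge trial the share of patients on the intervention rises with calendar time by design: none in the first period, all in the last. Unless the model contains period, it cannot separate the program from anything else that changed over the same months. The article recognises this for the primary outcome but writes a secondary-outcome list without the term.

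The hospital effect does not fill the gap. It shifts weight towards the before/after contrast within each hospital, which is where the calendar separation is largest. The rule on coincidental baseline differences does not fill it either: the imbalance in calendar time is built into the design, and period is not among the characteristics listed under Prognostic Factors.

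At stake are the effects on recovery, quality of life, self-efficacy, coping and pain. A steady improvement in usual care could be reported as benefit, and a steady worsening could hide one.

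**Working it through.** **Inputs from the article.** 9 hospitals, 10 periods of 2 months, one hospital crossing per step (Trial Design). From Sample Size: "With an intracluster correlation of .05, 9 clusters, and 10 time periods, the design effect is calculated to be 2.14", and about 5 patients per hospital per period. The article's total reproduces: 212 × 2.14 = 453.7, so 454, and 454/90 = 5.04 per cell. It states no figure for the secondary models.

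**Assumptions.** One outcome value per patient, total SD 1, no baseline covariate; the primary-outcome intracluster correlation carried over to the secondary outcomes; a linear calendar trend common to all hospitals; a true intervention effect of zero.

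**Step 1: calendar separation.** Hospital *i* is control in periods 1 to *i* (mean (*i*+1)/2) and intervention in periods *i*+1 to 10 (mean (*i*+11)/2). The difference is 10/2 = 5 periods, or 10 months, in every hospital. Over all cells the mean period is 3.67 for control and 7.33 for intervention, a gap of 3.67 periods.

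**Step 2: trend absorbed without period.** Generalised least squares on the 90 cell means with a random hospital intercept:

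- Within-cell variance s² = 0.95/5 = 0.19; between-hospital variance t² = 0.05.
- Weight θ = t²/(s² + 10t²) = 0.05/0.69 = 0.07246.
- There are 45 intervention cells; the squared numbers of intervention periods per hospital sum to 285; the period numbers over intervention cells sum to 330.
- A_xx = 45 − 285θ = 24.348; A_1x = 45(1 − 10θ) = 12.391; A_11 = 90(1 − 10θ) = 24.783.
- For a trend of 1 per period: A_xy = 330 − 45 × 55θ = 150.652; A_1y = 9 × 55(1 − 10θ) = 136.304.
- Expected intervention estimate = (A_xy − A_1x·A_1y/A_11)/(A_xx − A_1x²/A_11) = 82.50/18.152 = **4.545 periods**.
- SE = √(0.19/18.152) = **0.102 SD**.

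Across intracluster correlations the multiplier is 3.67 at 0, 4.03 at .01, 4.54 at .05, 4.74 at .10 and about 5.00 at .99.

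**Step 3: with period as a fixed effect.** The trend absorbed is 0. The variance, by the Hussey and Hughes formula with U = 45 and W = V = 285, is

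9 × 0.19 × 0.69 / [(9×45 − 285) × 0.19 + (45² + 90×45 − 10×285 − 9×285) × 0.05] = 1.1799/(22.8 + 33.0) = 0.02115,

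so SE = **0.145 SD**. The ratio is 0.1454/0.1023 = 1.42.

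**Step 4: consequence without period.** Bias = 4.545 × drift. Two-sided type I error = 1 − Φ(1.96 − bias/0.1023) + Φ(−1.96 − bias/0.1023).

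| Assumed drift per period (SD) | Total change, first to last period (SD) | Spurious effect (SD) | Type I error |
|---|---|---|---|
| 0 | 0 | 0 | 5% |
| 0.01 | 0.09 | 0.05 | 7% |
| 0.02 | 0.18 | 0.09 | 14% |
| 0.03 | 0.27 | 0.14 | 27% |
| 0.05 | 0.45 | 0.23 | 60% |

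A drift of opposite sign gives the same sizes in the other direction.

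**The case against.** The best defence is that the list is shorthand. The same sentence names no intervention term, no follow-up-time term and no patient-level random effect, all of which a longitudinal mixed model would need, and a journal article may leave such detail to a fuller plan. The authors' intent to adjust for calendar change is clear one paragraph earlier. This is a fair reason not to assume that period will in fact be left out. It does not clear the text: the article writes a specific list of adjustment variables and drops the one term that it has just justified for the same design.

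The figures also have limits, and these stand. The drift sizes are assumptions. The calculated model is simpler than the planned one, so its standard errors and error rates are illustrative. The intracluster correlation was chosen for the primary outcome. Baseline scores could absorb drift in case mix where they exist (the RI-10, EQ-5D and SF-36). They cannot absorb drift in postoperative care, and Table 3 as printed shows no preoperative measurement of pain, self-efficacy or coping.

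A reader might also infer that type of surgery is wrongly modelled as random. The wording does not support that firmly: the parenthesis may belong to hospital, as in the Cox model, and no effect on results has been shown.

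**Conclusion.** As written, the secondary-outcome models do not adjust for calendar time, although the design makes condition and calendar time move together and the primary analysis adjusts for it. The structural part is firm: 5 periods of separation within each hospital, and roughly 3.7 to 5 periods of any common linear trend passing into the estimate, whatever the intracluster correlation. The size of the harm is conditional, because the documents give no trend for any secondary outcome. Under the assumptions above it runs from nothing at zero drift to 0.23 SD and 60% type I error at 0.05 SD per period.

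Two stronger readings should be resisted. A reader might infer that the secondary effects will be biased in favour of the program. The documents establish neither that a trend exists nor its direction. A reader might also infer that the main conclusions fall with them. The adjusted Cox model contains period, and the Economic Evaluation section does not say that it uses these mixed models.

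**What to change.** Add time period, defined by the scheduled date of surgery, as a fixed effect in every secondary-outcome model, separate from weeks since surgery, and keep hospital as a random effect as in the adjusted primary model. If this was always intended, one sentence saying so is enough. In the same edit, state which term the random-effect parenthesis refers to.

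No new data are needed: allocation already depends on hospital and scheduled surgery date (Randomization), and the article reports that analysis had not begun at submission. The cost is precision: in the simplified calculation the SE rises from 0.102 to 0.145 SD, about 1.4 times. Period effects remove only the trend that hospitals share; trends that differ between hospitals would remain.
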